#### Sample size and sampling method

According to Nunnally & Bernstien, for a factor analysis in the validation of scales, 10 samples per item are required [31]. Given the 33 items in SCIB, 330 samples are needed. However, a sample of 660 people is required due to the sampling plan and the design effect of 2. Considering that the sampling plan in the first phase is cluster, the design effect must be considered. “The loss of effectiveness by the use of cluster sampling, instead of simple random sampling, is the design effect” [28]. Using a cluster sample usually needs a larger sample size than a simple random sampling and for a well-designed study, the design effect usually ranges from 1 to 3 [32, 33]. Considering a minimum 20% attrition rate, the total required sample size is calculated to be a minimum of 800 participants.

First, the rate of vaginal childbirth in public and private hospitals will be extracted separately. Then, all of the urban and suburban Tabriz health centers will be listed and numbered (114 centers). Using cluster sampling and the website www.random.org, approximately half of the centers will be randomly selected. A list of potential participants will be arranged based on the health records at each selected center. From the list, the required sample size for each center will be determined using the proportional sampling method by the rate of vaginal childbirth in public and private hospitals and the samples will be randomly selected. Using the phone number registered in each record, the researcher will call the potential participants and invite them to participate in the study.

The eligible participants will be provided with full explanations about the study objectives and procedures. Socio-demographic questionnaire, Childbirth Experience Questionnaire 2.0 (CEQ 2.0), and Support and Control in Birth questionnaire (SCIB) will be filled out in a relatively quiet environment by a research staff member and collected in person. A number of participants are likely to be illiterate, so the questionnaires will be completed by the researcher in order for the data collection method to be the same for all individuals. Obstetrics information will be collected by referring to individuals’ medical records. Also, informed consent will be obtained before collecting information from women’s medical records.

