SCIB contains 33 items and its subscales include internal control, external control, and support. The internal control contains 10 items that focus on the emotions, behavior, pain, and physical functioning (e.g. “I overcame my pain”). The external control contains 11 items that focus on pain relief, information, environment, decisions and procedures, and birth outcome (e.g. “I had control over when procedures happened”). The support contains 12 items that focus on coping methods, staff attitude, empathy and understanding, encouragement, listening, informational support, and support with pain relief (e.g. “The staff dismissed things I said to them”). Questions are scored on a 5-point Likert scale from agree completely to disagree completely. A score of 1 shows less control and support, and a score of 5 shows more control and support. Ten items are scored in reverse. SCIB will be completed 1 month after childbirth. The overall Cronbach’s alpha of the original SCIB has been reported 0.95. Also, the Cronbach’s alpha for internal control, external control, and support subscales has been reported 0.86, 0.93, and 0.93 respectively [21].

Due to the fact that the CEQ 2.0 and SCIB have not been validated in Iran, they will be standardized and validated prior to the start of the main study. The scales will be translated into Farsi using the Forward & Backward Translation method. The translated versions will be edited by two experts in concepts and the final versions will be created. For quantitative valuation of face validity, 20 postpartum mothers will complete the face validity checklist and will be asked to comment on clarity, simplicity, and relevance of items. Based on these notes, the translated items will be revised. The mothers will also be requested to comment on the impact score of the items on a 4-point Likert scale. To obtain the impact score, the percentage of mothers who score the items a value of 4 will be multiplied by the mean total impact score. Impact scores greater than 1.5 will be considered satisfactory [35].

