#### Data analysis

The data obtained in the first section of phase one will be analyzed using SPSS Statistics Version 25.0 for Windows (IBM Inc., Armonk, NY, USA). In the cross sectional stage, descriptive statistics will be used to describe the socio-demographic, antenatal and intrapartum factors and childbirth experience. The analytical statistics including univariate will be used to test the correlation between socio-demographic, antenatal and intrapartum variables with the childbirth experience. Then, variables with a correlation of *p* < 0.1 in the univariate analysis will be entered into the multivariable logistic model. All tests will be two-tailed. *P*-value <0.05 will be considered statistically significant. To promote data quality in the cross sectional stage, procedures such as double data entry and range checks for data values will be conducted.

The data obtained in the second section of phase one will be analyzed using SPSS Statistics Version 25.0 for Windows (IBM Inc., Armonk, NY, USA) and AMOS software. Construct validity will be measured using exploratory factor analysis and confirmatory factor analysis. In exploratory factor analysis, the Principal Axis Factoring method and oblimin rotation will be used to extract and rotate the factors. If the items loading are lower than 0.3, the item may be removed [37]. Next, exploratory analysis, confirmatory factor analysis will be used to support the findings of the scale dimensions. Indicators with acceptable values for the model to be approved include Root Mean Square Error of Approximation (RMSEA) < 0.08, Goodness of Fit Index (GFI), Comparative Fit Index (CFI) ≥ 0.90, and Normed chi-square ( x^2^/df < 5). Internal consistency will be assessed using the Cronbach’s Coefficient alpha. The test-retest reliability will be calculated through test-retest of 20 primiparous mothers with a 2 week interval and the calculation of Intra Correlation Coefficient (ICC).

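### The stated CFA approval rule uses only overall fit of one model, so it cannot by itself show that the SCIB or CEQ 2.0 dimensions are distinct

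*Protocol article*

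**What the plan says.** The Data analysis section for phase one of the protocol article plans an EFA first: "the Principal Axis Factoring method and oblimin rotation will be used to extract and rotate the factors". A confirmatory analysis follows, and its purpose is stated: "confirmatory factor analysis will be used to support the findings of the scale dimensions". Approval is then tied to numerical limits: "Indicators with acceptable values for the model to be approved include Root Mean Square Error of Approximation (RMSEA) < 0.08", followed by "Goodness of Fit Index (GFI), Comparative Fit Index (CFI) ≥ 0.90, and Normed chi-square" below 5. GFI has no limit of its own; I read the 0.90 as shared with CFI.

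The section names no competing model and no criterion on factor correlations. It gives no rule for how many factors the EFA retains, and does not say what happens if the EFA and the original subscales disagree.

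Under Scales and data collection, "SCIB contains 33 items and its subscales include internal control, external control, and support", with 10, 11 and 12 items. CEQ 2.0 has 23 items in four subscales. The same section says that neither scale has been validated in Iran.

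**The concern.** The conclusion sought is about dimensions, but the inputs to the rule are about overall fit. If the Farsi items of two or more subscales measure the same thing, a model that keeps them apart still reproduces the item correlations, with factor correlations estimated near 1, and every limit is met. The other planned statistics, Cronbach's alpha and the test-retest ICC, do not measure separation between subscales either.

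At stake is Objective 1, the psychometric properties of the two adapted scales. A passing CFA could be reported as support for three SCIB or four CEQ dimensions when the data support fewer. Any subscale scores reported later would then partly repeat one another.

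**Working it through.** **Sample size, to set N.** The plan starts from "Given the 33 items in SCIB, 330 samples are needed" (33 × 10). Doubling for the design effect gives 660; 660 × 1.2 = 792, rounded up to 800. After 20% attrition, 800 × 0.8 = 640. The point does not rest on these figures; they set the range of N for the checks.

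**Nesting.** The three-factor SCIB model has 33 loadings, 33 residual variances and 3 factor correlations, 69 parameters in all. With 33 × 34/2 = 561 variances and covariances, df = 492. The one-factor model has 66 parameters and df = 495. It is the three-factor model with all three correlations equal to 1. The three-factor chi-square therefore cannot be larger, whatever the data.

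**What the reported alphas imply for SCIB.** Overall, "alpha of the original SCIB has been reported 0.95"; by subscale, "internal control, external control, and support subscales has been reported 0.86, 0.93, and 0.93 respectively". With equal item variances, mean inter-item r = α/(k − (k − 1)α):
- internal control: 0.86/(10 − 7.74) = 0.381, loading √0.381 = 0.62
- external control: 0.93/(11 − 9.30) = 0.547, loading 0.74
- support: 0.93/(12 − 10.23) = 0.525, loading 0.72
- all 33 items: 0.95/(33 − 30.40) = 0.365

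Of 528 item pairs, 45 + 55 + 66 = 166 lie within subscales and 362 between. The mean between-subscale r is (528 × 0.3654 − 45 × 0.3805 − 55 × 0.5471 − 66 × 0.5254)/362 = 0.307. The mean loading product over those pairs is 0.482, so the implied factor correlation is 0.307/0.482 = 0.64.

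**The rule applied to simulated data.** Maximum-likelihood CFA, 60 replicates per setting, N = 660, 5-point items, loadings as above, no cluster effect. The three-factor mean CFI is 0.998 in every row.

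| True factor correlation | Three-factor model approved | One-factor model approved | One-factor mean CFI | Mean chi-square difference (3 df) |
|---|---|---|---|---|
| 1.00 | 100% | 100% | 0.998 | 2.9 |
| 0.95 | 100% | 100% | 0.991 | 92.1 |
| 0.90 | 100% | 100% | 0.969 | 300.9 |
| 0.85 | 100% | 0% (fails on GFI only) | 0.940 | 576.5 |
| 0.64 | 100% | 0% | 0.786 | 1941.7 |

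At a true correlation of 1.00 the three-factor means were RMSEA 0.006, GFI 0.956 and chi-square/df 1.03. Approval was also 100% at N = 330 and N = 800. The three-factor column never changes, so the rule carries no information about separation. The last two columns do.

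**The EFA as a guard.** The eigenvalue>1 rule is my assumption; the article states none. All data sets here have one true factor.
- SCIB-like loadings, N = 640: one factor was kept in 100% of runs with continuous or symmetric items and in 78% with skewed items.
- 33 items, loadings 0.5, 5-point items, N = 660: three or more factors in 60 of 60 runs.
- CEQ-like scale, N = 640: the subscale item counts are not given, so I assume 6, 6, 6 and 5. Alphas of 0.82, 0.62, 0.78 and 0.88 then imply loadings of about 0.66, 0.46, 0.61 and 0.77. Two or more factors appeared in 3% of runs (continuous), 20% (symmetric 4-category) and 49% (skewed 4-category), and in up to about 90% depending on skew.

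When the EFA-then-CFA path was run on one-factor data at N = 640, every over-extracted structure that could be fitted was approved. The mean CFI gain over one factor was about 0.000 to 0.005 in most settings and 0.015 in the worst.

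**The case against.** The strongest reply is that the EFA comes first and the CFA tests what it found. If the EFA returns one factor, no three-factor model reaches the CFA, so the 100% approval figures apply only once a multi-factor model has got that far. This stands, and it limits the point. A reader might infer that the plan will approve separate subscales whenever the items are one-dimensional. The document does not support that: at SCIB-like loadings and the planned N the EFA would usually return one factor. What remains is that the guard is not secured, because no retention rule is stated and extra factors are plausible with weaker loadings or skewed 4-category items.

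Second, nothing suggests that SCIB is one-dimensional. At the implied correlation of 0.64 the one-factor model is approved in 0% of runs. This also stands, but it describes the original scale; the Farsi version is what the validation must establish.

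Third, a reader might infer that the main results or the guideline are compromised. They are not shown to be. The objectives refer to the childbirth experience score, phase two selects women on the mean total score, and no section prespecifies a subscale test or passes subscale findings to the guideline.

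Fourth, the list of indicators is introduced as what they include, and a condensed article may leave model comparisons to a fuller plan. That is fair for omitted detail. Here, though, the article fixes a decision rule and its purpose, and the criteria it names cannot serve that purpose.

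**Conclusion.** The concern holds in a limited form. The four named indices cannot show that dimensions are distinct. This follows from nesting and does not depend on the simulation settings. How often it would mislead does depend on assumptions: an eigenvalue>1 rule, the CEQ item counts, loadings derived from the original alphas, equal item variances, no clustering, and above all item skew. For SCIB the exposure at the planned N is small unless items are skewed; for CEQ 2.0 it ranges from about 3% to 90% of one-factor data sets. The consequence is confined to the dimensionality conclusion under Objective 1 and any subscale-level reporting. It is a worthwhile improvement to the validation and does not threaten the total-score analyses.

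**What to change.** Add to the phase one Data analysis section: for each scale, the multi-factor CFA will be compared with a one-factor model and with models merging each pair of factors, using the chi-square difference and the change in CFI; factor correlations will be reported with 95% confidence intervals; separate dimensions will be claimed only if the overall limits are met and the multi-factor model fits materially better than the merged models; otherwise the total or merged score will be treated as the supported score.

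The authors should fix in advance what counts as materially better. The chi-square difference alone is not enough at this N: it averages 92 on 3 df at a true correlation of 0.95, where CFI changes by only 0.998 − 0.991 = 0.007. I would not impose a fixed ceiling of 0.90 on factor correlations, which missed many over-extracted structures when tried, nor require that only the merged score be reported.

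The cost is a few extra AMOS models on the same data and some wording, with no extra women. The downside is a possibly less favourable statement about the subscales. If the SCIB correlations are near 0.64, the comparison will simply confirm the three-factor structure.

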### Phase two: qualitative study

Phase two is an exploratory qualitative study with a conventional content analysis approach to explore women’s childbirth experiences in more detail.

#### Sample size and sampling method

Purposeful sampling will be used in phase two. The participants in this phase will be selected based on the mean total score of childbirth experience, which is collected in phase one of the study. Women with 10% upper and lower scores of childbirth experience will be selected as the extreme cases. We will seek to interview women with either a positive or negative childbirth experience to collect more comprehensive information about their childbirth experience and its effective factors.

The analysis process will be initiated from the first interview. The aim is to clarify the details and relationships between the pivotal concepts and categories derived from investigating the initial data. In this way, the selection of the participants will continue until the relationships between research concepts and variables, i.e. theoretical saturation, are determined [38]. In this study, the sampling will continue until the researcher felt no further information will be collected during data analysis and coding. Nevertheless, some references estimated 12 participants as the minimum number of participants required for a qualitative study [39].

#### Data collection

Qualitative data will be collected using individual in-depth, semi-structured interviews with open questions. Before implementing the qualitative phase, the questions in the interview protocol will be designed based on the findings of the first phase of the study and the literature review on the topic especially in developing countries.

The interviewer will be take notes in addition to the audio recording. If participants refuse to be audio recorded, solely notes will be used for data collection. During the interview, the interviewer will record non-verbal data such as tone of voice, facial expressions, and participants’ positions in a particular sheet with the date and place of the interview. Interviews will be conducted in one session for each person and will take up to 1 h [40]. The interviews will be conducted by the first author under the supervision of the research team, specifically the fifth author who is an expert in qualitative studies.

#### Data analysis

The qualitative data will be organized and managed with MAXQDA 12.13.1. Conventional approach to content analysis will be used in the qualitative phase of the study. This analysis is designed to categorise raw data into different classes or concepts based on valid deductions and interpretations. This process uses inductive reasoning, which presents concepts and classes through a precise investigation of data by the researcher [41].

In qualitative content analysis method, the three approaches; conventional, directed and summative are considered. In this study, qualitative content analysis will be used with a conventional approach. In this approach, data analysis begins by reading the entire text repeatedly to obtain a complete understanding of them. Then, texts are read word by word to extract codes by first underlining the exact words from the text that seem to obtain key concepts. Next, the text is made by the notes of first thoughts and initial analysis. Labels for codes emerge that are reflective of more than one key thought. These codes are then classified according to their differences and similarities. Ideally, 10 to 15 categories are sufficient for classifying a large number of codes. The main advantage of conventional content analysis is to obtain direct information from the study without imposing a predetermined category or theory. One challenge facing this type of analysis is its interference with other qualitative approaches, such as the grounded theory and phenomenology. Although these methods are similar in the initial analysis, they are prioritized over contractual content analysis for theory development. It is also useful for model development.^35^ In order to ensure trustworthiness of findings in the qualitative section, four criteria (credibility, reliability, portability and verifiability) were considered [42].

### Phase three: integration of quantitative and qualitative data/ and development of the guideline

In this phase the supportive evidence-based guideline for improving childbirth experiences among women will be developed by using a combination of literature review, the findings of two prior study phases and comments of experts.

To develop a guideline for the improvement of the childbirth experience, the research team will formulate the guideline initially through a comprehensive review of available evidence. The systematic review studies and interventional studies will be conducted to find approaches provided in available guidelines. Search will be done in the English language databases (Cochrane Library, MEDLINE, Web of Science, Embase, Scopus, ProQuest) and Persian (Magiran, SID and Barakat) using the keywords “Birth Experience”, “Labour Experience”, “Childbirth Experience”, “Delivery Experience”, “Maternal Experience”, “Mother’s Experience”, “Birth Satisfaction”, “Childbirth Satisfaction”, “Birth Perception”, “Childbirth Perception” from the inception of the databases until the time of search. Search strategy for Web of Science database will be as follows: (“birth experience*” OR “experience of birth*” OR “childbirth experience*” OR “experience of childbirth*” OR “labour experience*” OR “experience of labour*” OR “delivery experience*” OR “experience of delivery*” OR “mother’s experience*” OR “experience of mother*” OR “maternal experience*” OR “birth satisfaction*” OR “childbirth satisfaction*” OR “satisfaction of birth*” OR “satisfaction of childbirth*” OR “birth perception*” OR “perception of birth*” OR “childbirth perception*”) AND (intervention* OR “randomized controlled trial*” OR “RCT*” OR “randomized clinical trial*” OR “systematic review*” OR “meta-analysis*”).

The quality of relevant evidence will be assessed using GRADE, and then the evidence analysis will be done and recommendations will be formulated from the literature review. The recommendations produced will be delivered to the experts in the second round of the Delphi.

The combination of quantitative and qualitative results is usually carried out in three ways: integration into discussion, integration with a matrix or side by side display and transformation. In the present study, the method of integration into discussion will be used. In this method, findings from the qualitative and quantitative analyses are presented in the discussion. Some researchers who use this method present a paragraph that reports the quantitative results and continues the process with a paragraph related to qualitative results. Some others present descriptive quantitative results and then cite a quotation in the same paragraph to confirm the quantitative result. In another method which is not common, the process starts with quantitative findings and then presents a supportive descriptive quantitative finding [30, 43]. Findings from the integration of qualitative and quantitative findings are provided to the experts, as recommendations, in the second round of the Delphi.

Comments of experts will be collected using the Delphi method [44]. In the first round, the expert panel will be selected to participate in the Delphi stage. The experts will be selected purposively from those in the field of clinical service provision to women. All experts in the panel will be female in the fields of midwifery, obstetrics and gynecology, and fertility health. In the second round, the experts’ opinions about the effective factors of positive and negative childbirth experience will be collected using a questionnaire with open-ended items. The opinions of all experts will be coded and categorized. Then, the desired approaches will be obtained after the integration and removal of duplicated items. Other approaches obtained from the literature review and the integration of quantitative and qualitative results will be added to the approaches extracted from the experts’ opinions in the second round. Finally, all approaches will be prepared in the form of a statement in the third round. In this round, the experts will be asked to agree or disagree with each statement in terms of its effects on positive childbirth experience and feasibility/cost-effectiveness. The responses will be scored on a 5-point Likert scale ranging from 0 (completely disagree) to 4 (completely agree). The consensus score in this round will be 70%. The generally disagreed statements will be delivered once again, along with a statistical summary of responses from the previous stage. In the fourth round, the experts will be asked to give their final opinions about the remaining statements in the form of “I agree” and “I disagree.”

